### Statistical Analysis

Statistical analysis will be performed using SPSS version 25 (IBM Corp., Armonk, NY). Continuous data will be expressed as means (± standard deviation), with independent sample *t*-tests or the Mann-Whitney U test for between-group differences. Categorical variables such as causes of infertility and COH protocol will be represented as frequency and percentage and analyzed using the Chi-square test.

The pregnancy outcomes of the IGRA-positive and IGRA-negative groups will be compared using the Chi-square test. We will use multivariate logistic regression to adjust for the effect of baseline characteristics. Adjusted odds ratios, 95% confidence intervals, and *p*-values will be reported. A two-tailed *p*-value < 0.05 will be considered statistically significant.

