## Methods and Analyses

### Study Design

This is a prospective cohort study of infertile patients who will undergo IVF-ET from January 1, 2022, to December 30, 2024, at Peking University Third Hospital. According to the sample size calculation, ~1,200 participants will be enrolled. The inclusion criterion is untreated PTB on CXR. The exclusion criteria are (1) active TB, (2) a previous diagnosis of TB, (3) TB other than PTB (e.g., reproductive system TB, renal TB, lymphatic TB), (4) the presence of central nervous system diseases, cancer, or AIDS, (5) long-term oral corticosteroids, immunosuppressants, and inhaled corticosteroid therapy, which may increase the risk of TB, and (6) patients who lack decisional capacity or who cannot guarantee their participation until the end of the study (Table 1). Participants will be divided into IGRA-positive and -negative groups, and the pregnancy outcomes will be followed during pregnancy. We will investigate whether LTBI (positive IGRA) in patients with untreated prior PTB affects the pregnancy outcomes (Figure 1).

**Table 1 T1:** The inclusion and exclusion criteria for selecting the study participants.

**Primary inclusion criteria**	**Primary exclusion criteria**
• Age 18–45 years • Untreated prior PTB based on chest X-ray imaging findings	• Active TB•History of treated previous • TB other than PTB (e.g., reproductive system TB, renal TB, and lymphatic TB) • The presence of central nervous system diseases, cancer, or AIDS • Long-term oral corticosteroids, immunosuppressants, and inhaled corticosteroid therapy • Patients who lack decisional capacity or who cannot guarantee their participation until the end of the study

*AIDS, acquired immunodeficiency syndrome; PTB, pulmonary tuberculosis*.

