### Secondary Outcomes

The secondary outcomes include the numbers of retrieved oocytes, high-quality embryo rate, clinical pregnancy, number of active TB cases during pregnancy, and miscarriage (Table 3). Clinical pregnancy is determined upon observation of a gestational sac on ultrasonography. Miscarriage is defined as pregnancy loss before 28 weeks of gestation. The clinical pregnancy and miscarriage rates have been calculated as described earlier in this article (13, 23).

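### In a non-randomised cohort, the only stated tests that fit number of retrieved oocytes are unadjusted, and the adjusted model is not extended to high-quality embryo rate

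*Protocol article*

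**What the plan says.** The exposure groups are defined by a blood test, not by allocation. Under Study Design: "Participants will be divided into IGRA-positive and -negative groups, and the pregnancy outcomes will be followed during pregnancy".

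Under Secondary Outcomes: "The secondary outcomes include the numbers of retrieved oocytes, high-quality embryo rate, clinical pregnancy, number of active TB cases during pregnancy, and miscarriage". The first two of these, the oocyte count and the embryo rate, precede any pregnancy.

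The Statistical Analysis section then sets out two routes:

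- Continuous data are summarised by mean and SD, with t-tests or "the Mann-Whitney U test for between-group differences". Categorical variables go to a chi-square test.
- For pregnancy outcomes: "The pregnancy outcomes of the IGRA-positive and IGRA-negative groups will be compared using the Chi-square test". The next sentence adds: "We will use multivariate logistic regression to adjust for the effect of baseline characteristics". The output is named: "Adjusted odds ratios, 95% confidence intervals, and *p*-values will be reported".

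A single two-sided 5% threshold covers everything. The Sample Size Calculations section lists the adjusters for pregnancy outcomes (age, BMI, cause of infertility, stimulation protocol, endometrial thickness, good-quality embryo count) and bases the sample size on that 19-term logistic model.

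**The concern.** The plan accepts that IGRA-positive and IGRA-negative women may differ on factors that bear on outcome, since it adjusts pregnancy outcomes for age, BMI, cause of infertility and stimulation protocol. Those factors plausibly bear on oocyte yield at least as directly. Yet no adjusted method that suits a count is given, and nothing says that the logistic model also covers the embryo rate. Followed as written, the plan produces a crude comparison of oocytes between groups that were not randomised.

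At stake is the reading of the ovarian-response results. Strengths and Limitations says that the prospective design strengthens causal inference and that the results should support preventive treatment and guideline updates. A crude oocyte or embryo difference, which could be an age difference, would be read in that light.

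A smaller point concerns live birth. Both a crude chi-square test and an adjusted odds ratio are reported against the same threshold, and the text does not say which one decides.

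**Working it through.** **1. The plan's own figure.** Inputs from Sample Size Calculations: 19 model variables, 10 events per variable, live birth rate 30%, embryo transfer rate 53%.

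- Events: 19 × 10 = 190.
- Participants: 190 / (0.30 × 0.53) = 190 / 0.159 = 1,194.97, rounded up to 1,195, against about 1,200 stated.
- Forward: 1,200 × 0.53 = 636 transfers; 636 × 0.30 = 190.8 live births.

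The figure reproduces. It rests wholly on the adjusted logistic model; nothing is sized for the chi-square test.

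**2. Matching outcomes to methods.**

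| Outcome | Stated method that fits | Adjusted? |
|---|---|---|
| Live birth, clinical pregnancy, miscarriage | Chi-square, then logistic regression | Yes |
| Number of retrieved oocytes | t-test or Mann-Whitney | No |
| High-quality embryo rate | t-test or Mann-Whitney if treated as continuous; a binomial logit model would fit but is not stated | Not stated |

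The last two rows are an inference: the section names neither outcome beside any test. For the oocyte count, though, no other stated method fits.

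**3. How much a crude oocyte test could be distorted (illustration).** From the documents: N = 1,200 and 75.5% IGRA-positive (Introduction, unpublished prior data), giving 906 and 294 women. Assumed, not in the documents: every participant has a retrieval; oocyte SD 5 to 7; 0.2 to 0.4 fewer oocytes per year of age; mean age gap 0.5, 1 or 2 years; no true IGRA effect.

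- Bias = age gap × oocytes lost per year.
- SE = SD × √(1/906 + 1/294) = SD × 0.0671, which is 0.336 at SD 5 and 0.470 at SD 7.
- Rejection rate = 1 − Φ(1.96 − bias/SE) + Φ(−1.96 − bias/SE).

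| Age gap (years) | Low case: SD 7, 0.2 per year | High case: SD 5, 0.4 per year |
|---|---|---|
| 0.5 | 0.10 / 0.470 → 5.5% | 0.20 / 0.336 → 9.2% |
| 1 | 0.20 / 0.470 → 7.1% | 0.40 / 0.336 → 22.2% |
| 2 | 0.40 / 0.470 → 13.6% | 0.80 / 0.336 → 66.4% |

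With no age gap, and no other confounder, the rate is the nominal 5%.

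**4. The live-birth chi-square, for comparison.** 636 transfers split 75.5 : 24.5 give 480 and 156, assuming equal transfer rates in both groups. At a 30% live birth rate, SE(log OR) = √(1/(480 × 0.21) + 1/(156 × 0.21)) = 0.201. Assume a 1- to 2-year age gap and odds falling 5% to 10% per year. With no IGRA effect the crude OR is then between 0.95 (1 year at 0.95) and 0.81 (2 years at 0.90), and the test rejects in 5.7% to 18.2% of studies. This describes the crude test only; the adjusted analysis that follows it is there to remove this bias.

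**The case against.** The strongest reply has four parts.

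*The t-test and Mann-Whitney sentence is generic.* The examples in its paragraph are baseline descriptors, and an article may leave the model for each secondary outcome to a fuller document. It is true that assigning the oocyte count to that sentence is an inference. But the section does set out methods for between-group differences and does say where adjustment applies, and the stated adjustment does not reach a count outcome.

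*Logistic regression can handle the embryo rate.* This stands. A proportion of embryos can be modelled on the logit scale, so it would be wrong to say that the planned type of model cannot fit it. The point for this outcome is only that the plan does not say it will be used.

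*Live birth is adjusted.* This stands as well. A reader who stops at the chi-square sentence might infer that the primary outcome is left to a confounded test. The next sentence plans adjusted logistic regression, and the whole sample size is built on it. Giving crude results before adjusted ones is ordinary in a cohort study. Only an explicit statement of which analysis is primary is missing.

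*No age imbalance is shown.* This stands too. A reader might infer that IGRA-positive women will be older because infection accumulates with age, but the documents report no baseline factor by IGRA status. The defensible statement is that the groups may differ, and at the mild end of the illustration the error rate is close to nominal.

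**Conclusion.** The point holds for two secondary outcomes. For retrieved oocytes, the only stated tests that fit are unadjusted; for high-quality embryo rate, adjustment is possible with the type of model already named but is not planned in the text. Both sit oddly beside the adjustment that the plan requires for pregnancy outcomes.

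The size cannot be fixed from the documents. On the assumptions above, a crude oocyte test rejects in about 6% to 9% of studies at a half-year age gap, 7% to 22% at one year and 14% to 66% at two years, with no IGRA effect. These ranges rest on an assumed age gap, age slope and SD, on the 75.5% positivity carrying over, and on all 1,200 women having a retrieval. They show that the exposure is not negligible; they do not predict bias in this study.

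For live birth the documents do not support a charge of missing adjustment, and the 5.7% to 18.2% figure should not be read as the error rate of the study's primary analysis. What remains there is one clarifying sentence.

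**What to change.** In Statistical Analysis:

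1. Analyse number of retrieved oocytes by negative binomial (or linear) regression on IGRA status, and high-quality embryo rate by woman-level binomial (logit) regression with robust standard errors. Report adjusted estimates with 95% confidence intervals, and label the t-test or Mann-Whitney results as descriptive.
2. List the covariates of these two models by name, using pre-stimulation factors already collected, such as age, BMI and cause of infertility. Do not carry over the whole set from Sample Size Calculations: the good-quality embryo count is part of the embryo outcome, and it and endometrial thickness are measured after the exposure. A bare reference to baseline characteristics is not enough, because Table 2 has that title and includes retrieved oocytes and good-quality embryos.
3. State that the adjusted odds ratio from the logistic model is the primary analysis of live birth and that the chi-square test is descriptive.

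The cost is some wording and a little extra modelling. The sample size does not change and no new data are needed.

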### Patient and Public Involvement Statement

This is an observational study. The patient will be informed of all the procedures and will be asked to sign the informed consent voluntarily.

## Discussion

To the best of our knowledge, this is the first prospective study on the impact of positive IGRA on IVF-ET pregnancy outcomes in infertile patients with untreated prior pulmonary TB. We will enroll 1,200 participants and analyze whether positive IGRA will affect the pregnancy outcome of IVF-ET. The primary outcome is live birth rate. Secondary outcomes include the numbers of retrieved oocytes, high-quality embryo rate, clinical pregnancy, number of active TB cases during pregnancy, and miscarriage.

Identifying and treating individuals with a high risk of progression from LTBI to active TB disease is critical. Studies have indicated that untreated participants with a positive IGRA result have a 10.8-fold higher rate of progression to active TB (26). Moreover, higher IGRA values are closely related to disease progression (27). Preventive anti-TB treatment is needed for LTBI in high-risk patients (15, 16); these patients include those with human immunodeficiency virus infection; those on immunosuppression therapy for tumors, necrosis factor α inhibitors, or glucocorticoids; or those receiving organ or hematologic transplantation (15, 16). However, there is no study on whether preventive anti-TB treatment is needed for infertile patients who will undergo IVF-ET. The so-called “prior” or “old” pulmonary TB lesion on CXR cannot be determined inactive or non-active lesion based on imaging alone. Our previous study showed that the clinical pregnancy and live birth rates of patients with untreated prior pulmonary TB, which was detected by CXR, after IVF-ET were lower than those without prior pulmonary TB on CXR, especially in those with unexplained infertility (13). In addition, reactivation of TB during pregnancy may cause abortion and great harm to pregnant women and fetuses. In our previous study, we included cases of miliary TB during pregnancy and found that most patients (6/7) had untreated prior pulmonary TB detected by CXR screening before IVF-ET (unpublished data). Identifying high-risk groups of TB and how preventive anti-TB intervenes before pregnancy are worthy of attention.

Our hypothesis is that LTBI will affect pregnancy outcomes in infertile women receiving IVF-ET. Knowledge of the relationship between LTBI and pregnancy outcomes could provide evidence for clinical decision-making regarding anti-LTBI treatment in this population. If this hypothesis is verified, further studies will be carried out to evaluate anti-TB therapy for patients with LTBI. The standardized protocol of isoniazid with rifampicin for 3 months may be administered for these infertile patients with LTBI, and improvements in pregnancy outcomes will be explored in the future.

### Strengths and Limitations

The current study has several key strengths. First, our prospective study design, in which LTBI and pregnancy outcomes are reliably followed, will allow us to analyze the relationship between LTBI and pregnancy outcomes and provide stronger evidence for causality. The results of our study can offer insights into LTBI and IVF-ET outcomes within a country with an intermediate TB burden, such as China. The outcomes of our study will serve as strong evidence for preventive anti-TB treatment of LTBI in infertile women within a country with an intermediate TB burden and provide data for updating guidelines. Second, this is a prospective study designed by a multidisciplinary team of respiratory physicians, obstetricians, obstetrician-gynecologists, epidemiologists, statisticians, and other related experts, a collaborative effort to ensure the quality of the study.

The limitation of the study is that this is a single-center study in China, without multi-center participation. However, as one of the largest and most authoritative reproductive centers in China, we perform nearly 20,000 IVF-ET cycles annually. Moreover, the population in this study is from all over the country and is representative of the Chinese population. In addition, accepted standards are available for IGRA quality control and the IVF-ET process in the same single center.

## Ethics Statement

The studies involving human participants were reviewed and approved by Ethics Committee of Peking University Third Hospital. The patients/participants provided their written informed consent to participate in this study.

